# ACRNaCT trial protocol: efficacy of adjuvant chemotherapy in patients with clinical T3b/T4, N+ rectal Cancer undergoing Neoadjuvant Chemoradiotherapy: a pathology-oriented, prospective, multicenter, randomized, open-label, parallel group clinical trial

**DOI:** 10.1186/s12885-019-6289-6

**Published:** 2019-11-15

**Keywords:** Neoadjuvant chemoradiotherapy, Adjuvant chemotherapy, Locally advanced rectal cancer, Yield pathological stage

## Abstract

**Background:**

The CAO/ARO/AIO-94 demonstrated that neoadjuvant chemoradiotherapy (CRT) could decrease the rate of local recurrence rather than distal metastases in advanced rectal cancer. Adjuvant chemotherapy (ACT) can eliminate micrometastasis, and render a better prognosis to rectal cancer. However, adoption of ACT mainly depends on the evidence from colon cancer. Neoadjuvant CRT can lead to tumor shrinkage in a number of patients with advanced rectal cancer. The administration of adjuvant therapy depending on pretreatment clinical stage or postoperative yield pathological (yp) stage remains controversial. At present, the clinical guidelines recommend ACT for patients with stage II/III (ypT3–4 N0 or ypTanyN1–2) rectal cancer following neoadjuvant CRT and surgery. However, the yp stage may influence the guidance of ACT.

**Methods:**

According to the postoperative pathological stage, the present study was divided into two parts with different study design procedures. Patients will undergo different therapeutic strategies after collecting data related to postoperative pathological stage. For patients with pathologic complete response or yp stage I, the study was designed as a non-inferiority trial to compare the patients’ long-term outcomes in observational group and those in treatment group with 5-fluorouracil. For patients at yp stage II or III, the study was designed as a superiority trial to compare the oncological effect of oxaliplatin combined with 5-fluorouracil, in addition to 5-fluorouracil alone in ACT. The primary endpoint is 3-year disease-free survival (DFS). Secondary endpoints are 3-year, 5-year overall survival, 5-year DFS, and the rate of local recurrence and adverse events resulted from chemotherapy and the patients’ quality of life postoperatively.

**Discussion:**

The ACRNaCT trial aims to investigate whether observation is not inferior than 5-fluorouracil for pathologic complete response or yp stage I, and indicate whether combined chemotherapy contains superior outcomes than 5-fluorouracil alone for yp stage II or III in patients receiving neoadjuvant CRT and surgery for locally advanced rectal cancer (LARC). This trial is expected to provide individualized adjuvant treatment strategies for LARC patients following neoadjuvant CRT and surgery.

**Trial registration:**

The trial has been registered in ClinicalTrials.gov on January 30, 2018 (Registration No. NCT03415763), and also, that was registered in Chinese Clinical Trial Registry on November 12, 2018 (Registration No. ChiCTR1800019445).

## Background

Colorectal cancer is the third most commonly occurring cancer in men and the second most commonly occurring cancer in women worldwide. A recent study conducted on 36 types of cancer in 185 countries demonstrated that rectal cancer is the eighth most frequently diagnosed malignancy and the tenth most common cause of cancer-related mortality [1]. A Surveillance, Epidemiology, and End Results population-based rectal cancer analysis found that 72.20% of all rectal cancer patients with evaluable TN category were categorized as locally advanced rectal cancer (LARC; T3/T4 N0, TxN+) [2].

The therapeutic strategy for LARC has evolved over the past decades. The adoption of the principles of total mesorectal excision (TME) has yielded satisfactory survival outcomes, as well as decreasing local recurrence rate of mid-low rectal cancer. TME is the excision of the tumor en bloc with its blood and lymphatic supply, that is, the mesorectum. However, local recurrence and distant metastases have been still major causes of cancer-related mortality after TME.

The results of a randomized German CAO/ARO/AIO trial on preoperative chemoradiotherapy (CRT) demonstrated a decreased local recurrence and therapeutic toxicity compared with postoperative CRT [3, 4]. Adjuvant chemotherapy (ACT) has a potential for removing micrometastasis, as well as improving overall survival (OS). ACT has been well applied in colon cancer patients with high-risk stage II and stage III disease. After CRT, a number of rectal cancer patients experienced downstaging of T or N. It is difficult to distinguish real ‘high-risk’ stage II and stage III disease from yield pathological stage. A systematic review reported that ACT resulted in a reduction in the risk of recurrence (25%) and mortality (17%) [5]. However, limitations of this study were obvious. Only two randomized controlled trials enrolled patients who received neoadjuvant CRT. Oxaliplatin was not used in ACT. Besides, the value of ACT was susceptible to adjuvant radiotherapy. The results of EORTC 22921 trial revealed that ACT after preoperative radiotherapy was not associated with disease-free survival (DFS) or OS [6]. Similarly, no survival benefit was observed in another three trials [7–9]. A systematic review and meta-analysis of data obtained from the above-mentioned four trials reached similar conclusions [10]. However, insufficient compliance to ACT is identified as a main challenge to evaluate the value of ACT in patients with rectal cancer after neoadjuvant CRT and surgery.

Findings from adjuvant oxaliplatin in rectal cancer (ADORE) trial demonstrated that adjuvant oxaliplatin, leucovorin, and 5-fluorouracil (FOLFOX) could improve DFS compared with fluorouracil plus leucovorin in patients with LARC after neoadjuvant CRT and surgery. A subgroup analysis revealed that the survival benefit was only observed in pathological stage III rather than pathological stage II [11]. Pathological stage might be a predictive factor for guiding the choice of ACT. Results of CAO/ARO/AIO-04 trial also showed that DFS improved in patients who received oxaliplatin plus fluorouracil compared with those who received only fluorouracil [12]. At present, clinical guidelines do not make a robust proposal in favor of adoption of ACT for LARC patients after neoadjuvant CRT and surgery.

After CRT, patients may experience different levels of downstaging due to tumor heterogeneity, and about 20% of patients presented pathologic complete response. Multiple studies have demonstrated that tumor regression grade (TRG) is an independent prognostic factor [13–15]. Nevertheless, no clear evidence exists for TRG as a predictive marker for administration of ACT. A retrospective study reported the survival outcomes of patients who received neoadjuvant CRT, and experienced a pathologic complete response with the help of observation alone [16]. The 5-year DFS and OS rates of these patients were 96 and 100%, respectively. Similarly, results from the Surveillance, Epidemiology, and End Results database demonstrated that ACT seemed not to have survival benefit for rectal cancer patients with yield pathological (yp) Tis-2 N0 [17]. Furthermore, a pooled analysis of 3313 patients demonstrated that patients with a pathological complete response (pCR) after CRT may not benefit from ACT, while patients with residual lesion had slightly superior prognosis in the adjuvant setting [18]. However, evidence from National Cancer Database of Canada indicated that ACT was associated with better overall survival in patients with locally advanced rectal cancer who achieve a pCR. Stratified analysis revealed that only those patients with pretreatment node-positive disease benefited from administration of ACT [19]. A systematic review and meta-analysis included in 6 studies based on 18 centres or databases involving 2948 rectal cancer patients with pCR, and indicated that ACT is associated with improved OS in locally advanced rectal cancer patients with pCR after neoadjuvant CRT and radical surgery [20]. From the inspiration of these retrospective studies, we attempted to perform ACRNaCT trial to address the value of ACT in LARC patients who received neoadjuvant CRT and surgery.

## Methods/design

### Study design and participants

An Adjuvant chemotherapy in patients with clinical T3b/T4,N+ Rectal cancer undergoing Neoadjuvant Chemoradiotherapy (ACRNaCT) trial was conducted as a prospective, multicenter, randomized phase III study, consisting of two parts based on postoperative pathological stage. Overviews of enrollment and interventions are depicted in Fig. 1. Patients will be recruited from 29 Chinese institutions. Eligible patients will be diagnosed through magnetic resonance imaging (MRI) with T3b/T4,N+ rectal cancer and are histologically confirmed adenocarcinoma of the rectum (size of tumor < 10 cm from anal verge) without distant metastases. There will be no contraindications of anesthesia, operation, and CRT as well. Inclusion criteria include: (1) Age 18 to 75 years. (2) The lesion must be within 12 cm of the anus as measured by endoscopy. (3) Histologically confirmed diagnosis of rectal carcinoma. (4) Computed tomography (CT), MRI, and endoscopic ultrasound (EUS) verified as clinical stage III rectal cancer without involvement of other organs. (5) No evidence of multiple primary cancers. (6) Sufficient organ function. (7) Signed written informed consent form. Exclusion criteria include: (1) Younger than 18 or older than 75 years. (2) Synchronous or metachronous malignancy within 5 years. (3) Patients with intestinal obstruction, perforation or bleeding who require emergency surgery. (4) Patients with a history of pelvic irradiation. The American Society of Anesthesiologists (ASA) grade IV or V. (5) Women who are pregnant (confirmed by serum b-HCG in women of reproductive age) or breast feeding. (6) Severe mental disorders. (7) Patients with severe emphysema, interstitial pneumonia, or ischemic heart disease who cannot tolerate surgery. (8) Patients who received steroid therapy within one month. (9) Patients or family members misunderstand the conditions and goals of this study. The withdrawal criteria include: (1) Distant metastasis is confirmed by abdominal exploration or postoperative pathology. (2) Patients receive other treatment, which is not related to the present study. The situation that patients receive subsequent therapy after relapse or metastasis is permitted. (3) Patients with intestinal obstruction or perforation or bleeding who require emergency surgery after inclusion in the study. (4) Patients decide to withdraw from the study with any reasons. (5) Patients who cannot receive therapy any more due to non-neoplastic diseases. (6) Patients who cannot finish planed procedure due to any reasons.

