
**Fig. 1 Fig1:**
[figure not shown]
Overview of ACRNaCT trail

For patients with pCR or yp stage I, the study was designed as a non-inferiority trial to compare the long-term outcomes of patients in observational group and those in treatment group with 5-fluorouracil. For patients with yp stage II or III, the study was designed as a superiority trial of 5-fluorouracil in combination with oxaliplatin compared with 5-fluorouracil alone in adjuvant setting. Participants will be allocated 1:1 to an intervention group or a control group after obtaining pathological data. Recruitment initiated in November 2018 and is expected to be completed in December 2020. The trial has been registered in ClinicalTrials.gov on January 30, 2018 (Registration No. NCT03415763), and also, that was registered in Chinese Clinical Trial Registry on November 12, 2018 (Registration No. ChiCTR1800019445).

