### Adjuvant chemotherapy

According to postoperative pathological stage, patients with pCR or yp stage I will be randomly assigned (1:1) into two groups of observation and ACT with 5-fluorouracil. Patients with yp stage II or III will also be randomly assigned to (1:1) the treatment groups receiving either 5-fluorouracil or 5-fluorouracil plus oxaliplatin as ACT. The use of a course of three cycles of ACT is recommended. In 5-fluorouracil group, patients daily receive capecitabine (1250 mg/m^2^) twice for 14 days every 3 weeks orally. In 5-fluorouracil plus oxaliplatin group, adoption of XELOX (oxaliplatin (130 mg/m^2^) as a 2-h infusion on day 1, followed by daily capecitabine (1000 mg/m^2^) twice for 14 days every 3 weeks) or mFOLFOX6 (oxaliplatin (85 mg/m^2^), leucovorin (400 mg/m^2^), and fluorouracil (400 mg/m^2^) followed by continuous infusion of fluorouracil (2400 mg/m^2^) for 46–48 h, repeated every 2 weeks) is optional.

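### The withdrawal criteria take patients out of the study for not completing treatment, are not confined to the time before randomisation, and do not separate stopping treatment from leaving follow-up

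*Protocol article*

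**What the plan says.** The Study design and participants section of the Protocol article gives six withdrawal criteria. Three concern treatment that is not completed or not followed:

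- Treatment outside the trial: "2) Patients receive other treatment, which is not related to the present study"
- Treatment ended by other illness: "5) Patients who cannot receive therapy any more due to non-neoplastic diseases"
- Any other failure to complete: "6) Patients who cannot finish planed procedure due to any reasons"

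Criterion 3 adds emergency surgery for obstruction, perforation or bleeding after inclusion. Two other sentences bear on how far the list reaches. Criterion 4 reads "4) Patients decide to withdraw from the study with any reasons", so the list is about leaving the study. The exception attached to criterion 2 reads "The situation that patients receive subsequent therapy after relapse or metastasis is permitted".

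On timing, the text after Fig. 1 says "Participants will be allocated 1:1 to an intervention group or a control group after obtaining pathological data". The Adjuvant chemotherapy section says that "patients with pCR or yp stage I will be randomly assigned (1:1) into two groups of observation and ACT with 5-fluorouracil". For yp stage II or III the randomisation is between 5-FU and 5-FU plus oxaliplatin. Three adjuvant cycles are recommended.

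The Background says that "insufficient compliance to ACT is identified as a main challenge to evaluate the value of ACT in patients with rectal cancer". It gives no rate.

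**The concern.** Patients enter before chemoradiotherapy and are randomised only after surgery and pathology. The randomised adjuvant course therefore lies within the period in which someone may fail to finish or may take other treatment. If such a patient leaves the study, later recurrence and death need not be collected.

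The loss need not be equal between arms. In the non-inferiority part, observation has no chemotherapy to leave unfinished, so criteria 5 and 6 bear almost only on 5-FU. Criterion 2 can work the other way, by catching observation patients who take chemotherapy outside the plan. In the superiority part the arms differ by oxaliplatin, so completion may differ.

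If those who leave have a different prognosis from those who stay, the hazard ratio is shifted in the absence of any treatment effect. An intention-to-treat label in the analysis plan would not undo this: a patient whose follow-up has ended can only be censored, and that censoring would be informative.

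**Working it through.** **Reach of the criteria.** The exception to criterion 2 concerns therapy after relapse. DFS runs from surgery to recurrence (Outcomes), and randomisation follows pathology, so that criterion is meant to operate after randomisation. Criteria 5 and 6 carry no time limit. Criterion 1 (metastasis found at exploration or on pathology) acts essentially before randomisation and does no harm here.

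**Size.** The plan gives no withdrawal or completion rate, so there is no figure of its own to reproduce. What follows is an illustration.

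Inputs from the Sample size section: 3-year DFS of 85% on 5-FU, 192 per arm and margin 1.6 (non-inferiority part); 3-year DFS of 55% on 5-FU and 190 per arm (superiority part). Assumptions: no true treatment effect; a fraction q of an arm does not finish and is lost; non-finishers have r times the hazard of finishers; exponential times; 3 years of follow-up for everyone. Loss is placed at time zero. For an unfinished course that is close: three 3-week cycles last 9 weeks, against 156 weeks in 3 years.

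Formulas:
- Finishers' 3-year DFS, s, solves (1 − q)s + q·s^r = S, with S the arm's overall DFS.
- Apparent HR = ratio of ln(s) between arms.
- Events d = n(1 − q)(1 − s) per arm; SE of ln(HR) = √(1/d₁ + 1/d₂).
- P(non-inferiority) = Φ[(ln 1.6 − ln HR)/SE − 1.96].
- One-sided false superiority = 1 − Φ[1.96 + ln(HR)/SE].

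*Non-inferiority part, S = 0.85 in both arms, losses from 5-FU only.* With nobody lost, d = 192 × 0.15 = 28.8 per arm, SE = √(2/28.8) = 0.2635, and P = Φ(0.470/0.2635 − 1.96) = Φ(−0.176) = 43%. Worked case, q = 10% and r = 1.5: s = 0.856, HR = ln 0.85/ln 0.856 = 1.05, d = 28.8 and 24.8, P = 34%.

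| 5-FU lost | r | 5-FU DFS kept | HR observation/5-FU | Events | P(non-inferiority) |
|---|---|---|---|---|---|
| 0% | – | 0.850 | 1.00 | 57.6 | 43% |
| 10% | 1.5 | 0.856 | 1.05 | 53.6 | 34% |
| 10% | 2 | 0.862 | 1.09 | 52.7 | 28% |
| 30% | 1.5 | 0.868 | 1.15 | 46.6 | 20% |
| 30% | 2 | 0.881 | 1.29 | 44.7 | 10% |

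*The opposite direction, through criterion 2.* Take the plan's 75% on observation and 85% on 5-FU; the HR with everyone kept is ln 0.75/ln 0.85 = 1.77. Losing 10% of observation patients only gives 1.69 (r = 1.5) or 1.63 (r = 2). Losing 10% from each arm gives 1.77 or 1.78, so the two effects nearly cancel.

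*Superiority part, S = 0.55 in both arms.*

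| Lost, 5-FU / combination | r | DFS kept | HR combination/5-FU | Events | False superiority (one-sided) |
|---|---|---|---|---|---|
| 0% / 0% | – | 0.550 / 0.550 | 1.00 | 171.0 | 2.5% |
| 10% / 20% | 1.5 | 0.564 / 0.578 | 0.96 | 138.7 | 4% |
| 10% / 20% | 2 | 0.574 / 0.598 | 0.93 | 133.9 | 6% |
| 10% / 30% | 1.5 | 0.564 / 0.591 | 0.92 | 128.9 | 7% |
| 10% / 30% | 2 | 0.574 / 0.621 | 0.86 | 123.2 | 13% |

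With r = 1 the HR stays at 1.00 in both parts and only events are lost. In the superiority part, equal losses in the two arms also leave the HR at 1.00.

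**The case against.** The article lists criteria without saying what follows from them. A reader might infer that withdrawn patients are deleted and that the primary analysis compares completers. No sentence says so, and the analysis sets may well be defined in a full protocol or analysis plan that is not shown. This stands, and the point does not rest on a missing intention-to-treat definition. It rests on a printed rule that ties leaving the study to not completing treatment.

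Criteria 3, 5 and 6 can also be read as covering failure to complete chemoradiotherapy, consolidation or surgery, which is harmless before randomisation. The Resection section keeps patients who refuse surgery in the study, so criterion 6 is evidently not applied as automatic removal. Both remarks are fair. They show that the text is ambiguous, but they do not limit the criteria to the time before randomisation.

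The prognostic link is an assumption. DFS is defined up to recurrence, and comorbidity need not raise the recurrence hazard; with r = 1 there is no bias in the hazard ratio. It is equally unsupported to say that such withdrawals will be common: the Background describes earlier trials and gives no rate, and the course here is three cycles.

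Finally, the 43% starting value in the non-inferiority part reflects the few events expected from 192 per arm. That is a separate matter; only the fall from it belongs here.

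**Conclusion.** The criteria are wrong as written: criteria 2, 5 and 6, and criterion 3 where it occurs after randomisation, can take randomised patients out of the study, and nothing separates stopping treatment from ending follow-up. The resulting bias is possible, not demonstrated.

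In the superiority part its direction is towards the combination, provided that more combination patients fail to finish and that non-finishers do worse. Over the assumed range, one-sided false superiority is 4% to 13% instead of 2.5%. In the non-inferiority part a reader might infer that the rule must work against observation. That holds only if losses come mainly from 5-FU, when the chance of showing non-inferiority falls from 43% to between 34% and 10%. Criterion 2 can pull the other way, so the net direction is uncertain.

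All withdrawal fractions and hazard multiples are assumptions. This should be fixed; confidence is medium, because the handling of withdrawn patients may be set out in a document not shown.

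**What to change.** State that meeting a withdrawal criterion after randomisation does not end follow-up. Every randomised patient stays on the schedule in the Follow-up section, for recurrence and death, unless consent for follow-up itself is withdrawn. State that the primary analysis in both parts is by randomised arm, with a per-protocol analysis as support in the non-inferiority part. Record the reason and date of each withdrawal by arm, so that any imbalance can be seen.

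When treatment stops remains with the investigators; no treatment-stopping rule is proposed. The cost is a change of protocol wording and continued routine follow-up of patients who would otherwise have left. It is best done early, because outcomes that were never collected cannot be recovered at analysis.

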### Randomization process

The minimization technique will be used in the current trial. Stratification factors are age, yield pathological stage and distance from tumor to the anal verge. Patients will be randomly assigned using a central randomization system without masking.

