### Resection

Patients will undergo restaging 2 or 3 weeks after completion of neoadjuvant CRT. Surgery will be undertaken following principles of TME for patients who are appropriate for undergoing resection. For patients who have locally unresectable disease, additional chemotherapeutic cycles are needed. Alternatively, chemotherapy regimens can be changed. Watch-and-wait nonoperative approach is not recommended for clinical complete responders in terms of high-risk of recurrence. For patients who refuse undergoing surgery, the risk of relapse will be informed. These participants will not be excluded from our study and sustained clinical complete response for 12 months or longer should be reached under intensive surveillance.

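### Withdrawal criteria 5 and 6 are not confined to the period before randomisation and, read literally, withdraw randomised patients who do not complete adjuvant chemotherapy, so who stays in the trial can depend on arm

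*Protocol article*

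**What the plan says.** The Protocol article, Study design and participants, gives six withdrawal criteria. Criterion 5 is "Patients who cannot receive therapy any more due to non-neoplastic diseases". Criterion 6 is "Patients who cannot finish planed procedure due to any reasons". Criterion 2 covers treatment unrelated to the study, with one exemption: "The situation that patients receive subsequent therapy after relapse or metastasis is permitted". None of these three carries a time limit.

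The text after Fig. 1 places randomisation late: "Participants will be allocated 1:1 to an intervention group or a control group after obtaining pathological data". Randomization process adds: "Patients will be randomly assigned using a central randomization system without masking".

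Under Adjuvant chemotherapy, pCR/yp I patients are randomised to observation or 5-fluorouracil, and yp II/III patients to 5-fluorouracil with or without oxaliplatin. On duration it says: "The use of a course of three cycles of ACT is recommended". The Background names non-completion as a known problem: "insufficient compliance to ACT is identified as a main challenge to evaluate the value of ACT in patients with rectal cancer".

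**The concern.** Chemoradiotherapy and surgery are over by the time a patient is randomised. For a randomised patient, the treatment that can still be left unfinished is the adjuvant course. A site applying criterion 5 or 6 as worded could therefore withdraw a patient because of something that happens after allocation and depends on the allocated treatment. An observation patient has no adjuvant course to stop, while a patient on oxaliplatin has one more drug that may have to be stopped.

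If withdrawn patients then leave follow-up or the analysis, the groups compared for 3-year DFS are no longer the groups that were randomised. This affects both the non-inferiority and the superiority part. A later analysis plan can define the analysis set, but it cannot recover follow-up that a site ended under this rule.

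**Working it through.** **Step 1. Does the list reach past randomisation?** Criterion 1 (metastasis found at exploration or pathology) belongs before it, and criterion 3 (emergency surgery after inclusion) probably does. Criterion 2, however, exempts therapy after relapse. Outcomes counts DFS from surgery to recurrence, so relapse in that sense falls in follow-up, and the exemption would have little purpose if the list stopped at randomisation. Criteria 5 and 6 stand in the same list with no limit of their own.

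**Step 2. What does withdrawal end?** The article does not say. Criterion 4, the patient's own decision, speaks of leaving the study. An exemption for post-relapse therapy also makes most sense if withdrawal would otherwise end participation and not merely a short adjuvant course. Leaving the study is thus the more natural reading, but not the only one.

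**Step 3. Can it differ by arm?**
- pCR/yp I: unfinished adjuvant treatment under criteria 5 and 6 can occur in the 5-fluorouracil arm only.
- yp II/III: both arms have a course and one adds oxaliplatin, so rates may differ.

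**Step 4. How large could the effect be?** The article gives no withdrawal rate and no prognosis for withdrawn patients, so there is no stated figure to reproduce. What follows is illustration. Let S be the true 3-year DFS in an arm, w the share withdrawn from that arm only (assumed), and q the 3-year DFS of those withdrawn (assumed). Then

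retained DFS = (S − w·q)/(1 − w), and apparent HR = ratio of the logs of DFS (proportional hazards).

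*pCR/yp I.* Take S = 85% in both arms (the Sample size figure for 5-fluorouracil), so the true HR of observation to 5-fluorouracil is 1.00. Withdraw from the 5-fluorouracil arm only. Example: w = 20%, q = 75% gives (0.85 − 0.15)/0.80 = 0.875, and ln 0.85/ln 0.875 = 1.22.

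| w | HR if q = 75% | HR if q = 85% | HR if q = 90% |
|---|---|---|---|
| 10% | 1.09 | 1.00 | 0.96 |
| 20% | 1.22 | 1.00 | 0.92 |
| 30% | 1.43 | 1.00 | 0.86 |

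The margin is 1.6. Values above 1 make observation look worse, and values below 1 make it look better.

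*yp II/III.* Take 55% in both arms (the Sample size figure for 5-fluorouracil alone), so there is no true effect, with 190 per arm. Withdraw an extra share w from the oxaliplatin arm. The rejection rate uses the normal approximation with shift |ln HR|·√(D·a·(1 − a)), where D is the number of events and a the control share of retained patients. Example: w = 20%, q = 35% gives retained DFS (0.55 − 0.07)/0.80 = 0.60 and HR = ln 0.60/ln 0.55 = 0.854. D = 190 × 0.45 + 152 × 0.40 = 146.3 and a = 190/342 = 0.556. The shift is then 0.95 and two-sided rejection is about 16%.

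| w | q = 35%: HR, rejection | q = 45%: HR, rejection |
|---|---|---|
| 10% | 0.93, 7% | 0.97, 5.5% |
| 20% | 0.85, 16% | 0.93, 8% |
| 30% | 0.76, 35% | 0.87, 12% |

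Nominal rejection is 5%. If the same withdrawal falls on the control arm instead, the HRs at q = 35% become the reciprocals: 1.07, 1.17 and 1.32. If q = 55% there is no shift.

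**The case against.** The strongest objection is that the harmful step is not written down. The article does not say that withdrawn patients leave follow-up or the analysis, Follow-up sets visits with no stop on withdrawal, and the analysis population is commonly left to the full protocol or analysis plan. This stands. A reader might infer that the trial plans to drop non-completers from the analysis, or that a missing intention-to-treat statement is the fault. The document supports neither. The point is the stated rule, which permits the harmful reading.

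Second, the planned procedure could mean chemoradiotherapy and surgery, and three cycles are only recommended, so stopping after two is not plainly a failure to finish. This is arguable, and it is why the wording has to settle the matter. It helps less with criterion 5, which speaks of therapy in general.

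Third, some tempting extensions do not hold:
- A reader might take criterion 2 to cover dropping oxaliplatin, moving between capecitabine and fluorouracil, or giving capecitabine to an observation patient. These are all study drugs, and the criterion concerns treatment unrelated to the study. It remains a secondary concern, limited to non-study treatment before relapse.
- Resection says of patients who refuse surgery that "These participants will not be excluded from our study". A reader might infer that other deviators are excluded. The sentence retains patients at a stage before randomisation and says nothing about those who stop adjuvant chemotherapy.
- A reader might want a loss from 80% power in pCR/yp I. There is no coherent base for it: 85% against 75% implies HR = ln 0.75/ln 0.85 = 1.77, already beyond the 1.6 margin.

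Finally, the withdrawal rates and prognoses above are invented and the shift runs both ways. That is correct. The figures show what could happen and are not an estimate of bias.

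**Conclusion.** The point holds for criteria 5 and 6. As worded they can withdraw randomised patients for not completing adjuvant chemotherapy. In pCR/yp I this can happen in one arm only, and in yp II/III it may happen at different rates, in an unmasked trial whose own background expects poor compliance. The 3-year DFS comparison is exposed to post-randomisation selection if sites apply the criteria literally and withdrawn patients leave follow-up or the analysis.

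Direction and size cannot be set from the document. Over the assumed ranges, an HR of 1.00 in pCR/yp I reads between 0.86 and 1.43, and a null result in yp II/III is rejected in 5.5% to 35% of trials. There is no distortion if withdrawn patients have the same prognosis as the rest of their arm. The wording should be amended. Confidence is medium, because the article does not spell out what withdrawal ends.

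**What to change.** Amend the withdrawal criteria in Study design and participants so that criteria 2, 5 and 6 count as withdrawal from the study only before randomisation. Suggested text for the period after it:

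> After randomisation, stopping adjuvant chemotherapy early, changing it, or receiving other treatment is recorded, with the reason, as discontinuation of or deviation from assigned treatment. The patient remains in DFS and OS follow-up and is analysed in the randomised arm. Only withdrawal of consent to follow-up ends follow-up.

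The cost is a short amendment, an eCRF field for the reason, and continued follow-up of patients who have stopped treatment. The statistical price is dilution: keeping non-adherent patients in their arm shrinks any treatment difference, which in the non-inferiority part can favour observation. A supportive per-protocol analysis there would show how far the conclusion depends on adherence.
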